### Sample size {14}

A priori sample calculation was performed in the Gpower 3.1.5 software, considering the comparison of two independent groups (control and intervention) in four distinct stages (pretreatment, 13th and 18th assessment, and follow-up). The statistical test that will be applied was also taken into account, that is, repeated measures analysis of variance (ANOVA) for the variables of interest (pain, manual dexterity, function, strength, and muscle activation). It was considered an effect size of 0.25, 5% significance, and power of 90%, resulting in 46 participants (23 per group). Considering possible sample losses, we will evaluate 20% more, that is, 56 subjects divided into two groups of 28 each.

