### Outcomes {12}

#### Primary outcomes

The primary outcomes will be change in pain scores at the base of the thumb, assessed by VAS (0–100 mm), at rest and during pinch movement from baseline to 6 weeks [30]; change in hand function, evaluated using the Australian/Canadian Hand Osteoarthritis Index (AUSCAN) (0–36) from baseline to 6 weeks [30]; change in values of pinch strength (Lafayette Hydraulic Pinch Gauge (in kg)) from baseline to 6 weeks; and change in magnitude of activation of the abductor pollicis brevis (APB), 1st DI, extensor pollicis brevis (EPB), and abductor pollicis longus (APL) from baseline to 6 weeks.

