## Statistical methods

### Statistical methods for primary and secondary outcomes {20a}

Data will be analyzed according to the intention-to-treat principle. All trial outcomes will be blinded for treatment allocation, and all participants will be analyzed in the treatment group to which they were originally randomized. Statistical analysis will be performed using the Statistical Package for the Social Sciences, version 19.0 (SPSS Inc., Chicago, IL, USA). A 5% significance level will be adopted for all analyses. The normality of the residues will be verified by the Shapiro-Wilk test. Pain, function, activity and participation, grip and pinch strength, dexterity, and muscle activation will be compared between the groups (control and intervention) and stages (pretreatment, 4- and 6-week assessments, follow-up), and interactions between them analyzed by mixed model ANOVA considering group and time factors for repeated measures if the residuals exhibit normality with post hoc contrasts (treated versus control group).

The first statistical procedure will be to verify, in general and at each assessment stage (pretreatment, 13th and 18th assessment, follow-up) if pain, function, activity and participation, grip and pinch strength, dexterity, and muscle activation differ between the intervention and control groups. The second statistical procedure aims to verify whether pain, function, activity and participation, grip and pinch strength, dexterity, and muscle activation change over the four assessment stages (pretreatment, 4- and 6-week assessments, follow-up) within each group.

The quantitative variables will be expressed as minimum and maximum values, means, medians, standard deviations, coefficients of variation, and asymmetry coefficients. Categorical variables will be expressed as frequencies and percentages.

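### The 46 participants for 90% power do not follow from the stated four-stage inputs, and the 90% does not describe the primary week-6 comparison

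*Protocol article*

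**What the plan says.** The Sample size section of the protocol article gives a complete calculation with its result. The tool: "A priori sample calculation was performed in the Gpower 3.1.5 software". The design: "considering the comparison of two independent groups (control and intervention) in four distinct stages (pretreatment, 13th and 18th assessment, and follow-up"). The test: "repeated measures analysis of variance (ANOVA) for the variables of interest", which the section lists as pain, manual dexterity, function, strength and muscle activation. The result: "It was considered an effect size of 0.25, 5% significance, and power of 90%, resulting in 46 participants (23 per group"). The allowance for losses: "Considering possible sample losses, we will evaluate 20% more, that is, 56 subjects divided into two groups of 28 each".

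The Primary outcomes section defines pain as a change "at rest and during pinch movement from baseline to 6 weeks", and uses the same baseline-to-week-6 interval for AUSCAN function, pinch strength and muscle activation. The statistical methods section plans a mixed ANOVA with group and time factors, their interaction and post hoc group contrasts, and says "A 5% significance level will be adopted for all analyses".

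Table 1 and the Four-week assessment section schedule no grip strength, pinch strength, BULFT or muscle activation at week 4. By that schedule these measures have three stages. The Secondary outcomes section nevertheless lists week-4 changes for them.

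**The concern.** A sample size paragraph should let a reader recover its number and see what the stated power refers to. This one allows neither. The two settings that drive a repeated measures calculation most, the tested term and the within-person correlation, are absent, and under the common working value of 0.5 the stated inputs do not return 46. The calculation is also applied to all variables as if each had four stages, and it concerns an omnibus ANOVA term, whereas every primary outcome is a between-group difference in change at one time point.

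What is at stake is how the result will be read. The comparison is between two active exercise programmes, and the Discussion says that, absent superiority, the trial will determine whether the programmes are equivalent. Readers would take a null week-6 result as coming from a trial with 90% power for a medium effect. If a moderate difference is the one of interest, that is not so.

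**Working it through.** **Inputs from the protocol:** 2 groups, 1:1; m = 4 stages; effect size 0.25, read as Cohen's f; α = 0.05; power 0.90; N = 46.

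**Assumptions (not in the protocol):** correlation ρ equal between all pairs of visits, base case 0.5; sphericity (ε = 1); two-sided testing for the week-6 contrast. SD means the SD of a single score, equal at all visits.

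**Step 1: the stated N.** Noncentral F:

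- Interaction: λ = f²·N·m/(1 − ρ), df = (m − 1) and (N − 2)(m − 1).
- Group effect: λ = f²·N·m/(1 + (m − 1)ρ), df = 1 and N − 2.

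| Term | Stages | ρ | Smallest even N for 90% | Power at N = 46 |
|---|---|---|---|---|
| Interaction | 4 | 0.5 | 30 (λ = 0.0625·30·4/0.5 = 15.0; 90.3%) | 98.6% |
| Group effect | 4 | 0.5 | 108 (λ = 0.0625·108·4/2.5 = 10.8; 90.3%) | 55.5% |
| Interaction | 2 | 0.5 | 46 (λ = 0.0625·46·2/0.5 = 11.5; N = 44 gives 89.97%) | 91.2% |
| Interaction | 4 | 0.20 | 48 | 89.5% |
| Interaction | 4 | 0.23 | 46 (N = 44 gives 89.3%) | 90.7% |
| Interaction | 4 | 0.25 | 44 | 91.5% |
| Group effect | 4 | 0 | 46 (N = 44 gives 89.97%) | 91.2% |

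So 46 reproduces directly with two measurements. With four stages and sphericity it needs ρ of about 0.22 to 0.24 (interaction) or ρ = 0 (group effect).

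A sphericity correction is a further possible route. The four-stage interaction at ρ = 0.5 needs 38 at ε = 0.75 and 50 at ε = 0.5, so an ε in between also returns 46. With λ and both df multiplied by ε, ε = 0.55 gives 90.4% at N = 46 and 89.0% at N = 44. The protocol mentions no such correction.

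**Step 2: outcomes with three stages.** Put m = 3 and N = 46 into the settings that make four stages return 46:

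- Interaction, ρ = 0.22 to 0.24: 84.2% to 85.2%.
- Group effect, ρ = 0: λ = 0.0625·46·3 = 8.625, power 81.9%.
- Interaction, ρ = 0.5, ε = 0.55 also at three stages: 84.5%.

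Under each of these settings the 90% does not carry over to outcomes measured three times.

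**Step 3: what f = 0.25 means at week 6.**

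- Interaction, two times: a difference in change of δ SD gives interaction effects of ±δ/4, so f = δ/4 and δ = 1.0 SD.
- Interaction, four stages, equal difference at all post-baseline visits: f = (δ/2)·√(0.75·0.25) = 0.2165δ, so δ = 1.15 SD. Other time patterns examined give 0.89 to 1.41 SD at week 6.
- Group effect: f = d/2, so d = 0.5 SD.

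**Step 4: power for the week-6 contrast.** Two-sample noncentral t on the change score, with noncentrality δ·√(n/2)/√(2(1 − ρ)) and 2n − 2 df. For δ = 0.5, n = 23, ρ = 0.5: 0.5·√11.5/1 = 1.696, power 38%.

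| Difference in change | n per group | ρ = 0.3 | ρ = 0.5 | ρ = 0.7 |
|---|---|---|---|---|
| 0.5 SD | 23 | 29% | 38% | 57% |
| 0.5 SD | 28 | 34% | 45% | 66% |
| 1.0 SD | 23 | 80% | 91% | 99% |

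At ρ = 0.5 and n = 23, 90% power needs a difference of 0.98 SD. If the analysis adjusted for baseline (variance factor 1 − ρ² = 0.75), it would need 0.85 SD, and power for 0.5 SD would be 48% (56% with 28 per group).

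**The case against.** The strongest reply is that no arithmetic error has been shown. The protocol does not give the correlation, and there are values at which four stages, f = 0.25 and 90% return 46. A condensed article may leave the correlation and sphericity setting to a fuller document. This stands in part: a reader might infer that 46 is impossible with four stages, or that the software was run with two measurements by mistake, and the text supports neither. What remains is that 46 cannot be recovered from the inputs printed, and that the settings which do return it undercut the 90% for outcomes with three stages.

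A reader might also infer that the trial has only 30% to 60% power for an effect of the size stated. That does not follow. It is true only if 0.25 is converted to a 0.5 SD between-group difference. Since the planned analysis contains a group-by-time term, the interaction reading is at least as natural, and under it the effect is about 1 SD, with week-6 power of about 91% at 23 per group and ρ = 0.5. Even for 0.5 SD the range is wider than 30% to 60%: 66% for a change score at 28 per group and ρ = 0.7, and up to 73% with baseline adjustment there.

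The loss allowance could look wrong as well, because 46/0.8 = 57.5 exceeds 56. But the protocol says it adds 20%, and 46 × 1.2 = 55.2 rounds up to 56, as worded. It does not promise 46 completers after a 20% loss. That is a matter of convention.

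**Conclusion.** The point holds in this form. The 46 does not follow from the inputs given: at ρ = 0.5 with sphericity they lead to 30 or 108, depending on a term the protocol does not name, and 46 matches two measurements. The settings examined that return 46 with four stages leave three-stage outcomes at about 82% to 85%, so a single 90% for all listed variables is not supported. That part relies on Table 1 and the Four-week assessment section for the number of stages, and the Secondary outcomes section disagrees with them.

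Separately, the sized term is not the primary comparison. If the interaction was powered, the 90% belongs to a difference in change of about 1 SD between two exercise programmes. For 0.5 SD at week 6, power with 46 evaluable participants is about 38% at ρ = 0.5 (29% to 57% for ρ from 0.3 to 0.7). These figures rest on an assumed correlation and an unadjusted change-score contrast. The direction does not depend on the exact value: no correlation from 0.3 to 0.7 brings 0.5 SD near 90%.

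**What to change.** Keep 56 participants and rewrite the paragraph around the primary contrast, for example: with 46 evaluable participants the trial has 90% power (two-sided 5%) for a between-group difference in change from baseline to week 6 of about 0.98 SD, assuming a correlation of 0.5 between visits; for 0.5 SD the power is about 38%. Use 0.85 SD and 48% only if the planned analysis is changed to adjust for baseline, which the statistical methods section does not currently provide for.

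If the ANOVA calculation is kept alongside, state the tested term, the number of measurements, the assumed correlation, any sphericity correction and the effect-size convention. Do not claim the same power for outcomes measured at three stages, and reconcile Table 1 and the Four-week assessment section with the week-4 changes listed under Secondary outcomes.

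The cost is one paragraph and no extra participants. The stated power becomes less favourable, but it then describes the comparison on which the trial will be judged.

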### Recruitment {15}

Participants will be recruited from social media, local and regional orthopedic and rheumatology clinics, newspaper and magazine advertisements, and leaflets posted on bulletin boards and dissemination in the university’s internal media.

### Intervention assignment: allocation

#### Sequence generation {16a}

Individuals who agree to take part in the study and meet all the study criteria will be assigned to the intervention or control group by 1:1 allocation, according to computer-generated randomization, using block sizes of 4 and 6. The two physiotherapists who will apply the interventions will also be randomized in order to avoid bias in blinding.

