### Interventions

#### Explanation for the choice of comparators {6b}

The intervention group will perform manual thumb joint mobility and 1st DI strengthening exercises. The control group will be submitted to a standard manual exercise protocol with proven benefits, previously published in the literature. All the sessions for both groups will be carried out in person, on non-consecutive days, with one of the two physiotherapists trained to apply the protocols.

The intervention will take place over a 6-week period, with three 45-min sessions a week, totaling 18 treatment sessions. The first session will take place 1 week after the baseline assessment. Both intervention protocols will be applied based on the shaping method for exercise load progression, as described below.

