#### Implementation {16c}

All patients who give consent for participation and who fulfill the inclusion criteria will be assigned to the intervention group or control group through a 1: 1 allocation, according to computer-generated randomization, using blocks of sizes 4 and 6. A Master’s student not involved in participant assessment will prepare the sequence generation and envelopes. The study coordinator will open the envelopes only after the enrolled participant completes all baseline assessments. The estimated time between baseline assessments and allocation will not exceed 5 days. The envelopes will identify the physiotherapist to perform the intervention and which intervention the participant has been assigned to.

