### Assignment of interventions: blinding

#### Who will be blinded {17a}

All clinical assessments will be conducted by an evaluator blinded to treatment allocation. In order to reduce blindness bias, participants will be instructed not to disclose any information about the treatment received during reassessment. In the event of unblinding of the assessor, its occurrence and the reason for it will be recorded and reported along with the trial results.

The two physical therapists who will coordinate the treatments will not be blinded to the group allocation, since both professionals will implement the two protocols. The statistician involved in the analysis will be blinded to the group allocation.

Participants will be blinded to the study hypothesis and their group allocation, but rather advised of the overall aspects involved in the treatment of both groups. They will not be informed of the specific treatments applied to each group or of the intergroup differences.

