### Methods for additional analyses (e.g., subgroup analyses) {20b}

No additional analysis will be performed.

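### Each participant is randomised to one of two physiotherapists as well as to an arm, but the stated model has only group and time, which costs a little precision

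*Protocol article*

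**What the plan says.** Four statements in the protocol article fix the design on this point.

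- Sequence generation {16a}: participants are allocated "by 1:1 allocation, according to computer-generated randomization, using block sizes of 4 and 6", and then "The two physiotherapists who will apply the interventions will also be randomized in order to avoid bias in blinding".
- Implementation {16c}: "The envelopes will identify the physiotherapist to perform the intervention and which intervention the participant has been assigned to". The physiotherapist is therefore assigned per participant, together with the arm. Envelopes are opened only once baseline assessments are complete.
- Who will be blinded {17a}: the physiotherapists are not blinded, "since both professionals will implement the two protocols". Physiotherapist is crossed with arm, not nested in it.
- Explanation for the choice of comparators {6b}: the 18 sessions are given in person "with one of the two physiotherapists trained to apply the protocols".

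The analysis section, {20a}, names the model: a "mixed model ANOVA considering group and time factors for repeated measures", with the group-by-time interaction and post hoc contrasts between arms. Physiotherapist does not appear there or in Sample size {14}.

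**The concern.** The allocation has two randomised factors and the model uses one. Treatment is 18 face-to-face sessions in which the physiotherapist supervises exercises with individual load progression, so some difference between the two in pain, function or strength is plausible. With no term for it, that difference stays in the error against which the arms are compared. At stake are a slightly wider confidence interval, slightly lower power, and a result that does not show whether outcomes differed by who delivered the treatment.

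The form of the term also matters. The physiotherapist is revealed only after baseline and the primary outcomes are changes from baseline to 6 weeks. A physiotherapist effect can therefore only emerge over time, and a main effect alone in the repeated-measures model would not remove it from the test of group by time.

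**Working it through.** **Inputs from the protocol article:** two physiotherapists crossed with two arms; 28 participants per arm (56 in total); 46 before losses, at effect size 0.25, 5% significance and 90% power; four assessments. **Assumption:** a difference d between physiotherapists of 0.3 to 0.5 residual SD. The documents give no value.

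**1. The plan's own sample size.** In a noncentral F calculation, N = 46 is reproduced for the between-groups effect with four measurements and correlation 0 (power 0.912). It is also reproduced for group by time with four measurements and correlation about 0.22 to 0.24. The article does not state the correlation, and this point does not depend on it. Adding 20% gives 46 × 1.2 = 55.2, rounded up to 56 as stated.

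**2. Extra residual variance if the term is omitted.** With an equal split between physiotherapists, the added variance is d²/4 of the residual variance.
- d = 0.3: 0.09/4 = 0.0225, about 2%.
- d = 0.5: 0.25/4 = 0.0625, about 6%.

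**3. Standard error of the arm difference.** Without the extra variance it is √(2/28) = 0.267 SD.
- d = 0.3: multiplied by √1.0225 = 1.011, giving 0.270 (about 1% more).
- d = 0.5: multiplied by √1.0625 = 1.031, giving 0.275 (about 3% more).

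In participants, 56 × 0.0225/1.0225 = 1.2 and 56 × 0.0625/1.0625 = 3.3.

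**4. Power.** Start from a nominal 90%, where 1.960 + 1.282 = 3.242, and let the physiotherapist explain a share R² of the total variance. Power is then Φ(3.242 × √(1 − R²) − 1.960), and the N that restores 90% is 46/(1 − R²).

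| R² (assumed) | Power without the term | N to restore 90% |
|---|---|---|
| 1% | 89.7% | 47 |
| 5% | 88.5% | 49 |
| 10% | 86.8% | 52 |

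The range d = 0.3 to 0.5 corresponds to R² = 0.0225/1.0225 = 2.2% to 0.0625/1.0625 = 5.9%, inside this table.

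**5. Validity.** A two-arm comparison with two crossed physiotherapists was simulated, 6,000 runs per setting. With 23 per arm and physiotherapists balanced within arm, type I error without the term was about 0.047, 0.045 and 0.038 at R² = 1%, 5% and 10%. With the term it was about 0.05. With physiotherapists assigned by simple randomisation it was about 0.05 either way. With the term, power in the balanced setting stayed at about 0.88 to 0.89, the same as with no physiotherapist effect.

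**6. Form of the term.** Suppose the difference is 0 at baseline and d at each of the three later assessments. The profile (0, d, d, d) has mean 0.75d and deviations (−0.75d, 0.25d, 0.25d, 0.25d). A main effect absorbs the mean only. The deviations stay in the error of the group-by-time test unless physiotherapist by time is fitted, at 4 − 1 = 3 degrees of freedom. In a model of change to 6 weeks the effect is a single number per participant, so one degree of freedom suffices.

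**The case against.** The strongest reply is that nothing here is invalid. The physiotherapist is randomised to protect blinding and is not declared a stratification factor. An unadjusted comparison of randomised arms is legitimate, and adjusting is a choice about efficiency. An analysis plan not shown could add the term. The statement under {20b} that "No additional analysis will be performed" concerns subgroup-type analyses and does not forbid a factor inside the main model. The size of the loss rests wholly on an assumed difference between two people trained in the same protocols.

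Most of this stands, and it is why the point is minor. What remains is that {20a} names its model factors and leaves out one that the allocation itself creates.

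A reader might infer two stronger things.

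- *That uneven physiotherapist shares shift or confound the arm comparison.* If physiotherapist is assigned independently of arm, the SE of the difference in shares is √(2 × 0.25/28) = 0.134, and 0.134 × 0.5 SD = 0.067 SD. But this is the variance from step 2 seen again: 2 × 0.0625/28 = 0.00446, and √0.00446 = 0.067. The ordinary standard error already carries it. It is not bias and not a second harm.
- *That the block sizes fail to balance physiotherapists within arm.* The article ties blocks of 4 and 6 to the 1:1 allocation of arms. It does not describe how physiotherapists are randomised, so neither balance nor imbalance can be read from it.

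**Conclusion.** The point holds as a modest, nearly free gain in precision. Each participant is randomised to an arm and to a physiotherapist, the two are crossed, and the stated model uses only arm and time. For an assumed physiotherapist difference of 0.3 to 0.5 SD, omission raises residual variance by about 2% to 6% and the standard error of the arm difference by about 1% to 3%. Over an assumed variance share of 1% to 10%, power falls by about 0.3 to 3 percentage points. If the physiotherapists do not differ, nothing is lost. The documents do not support a claim of bias, confounding or inflated type I error, and the planned sample size does not need to change.

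**What to change.** Add to {20a}, before any outcome is examined by arm, one of the following:

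- in the repeated-measures model, physiotherapist (two levels, as named in the envelope) and physiotherapist by time as fixed effects; or
- for the primary outcomes, a physiotherapist main effect in a model of change from baseline to 6 weeks.

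Use fixed effects, since two physiotherapists are too few to estimate a random-effect variance. Classify each participant by the physiotherapist named in the envelope. Also report outcomes by physiotherapist within arm, as description without a test.

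The cost is small. With 56 participants and four assessments, the first option takes 1 degree of freedom from the between-participant error (54 to 53) and 3 from the within-participant error (54 × 3 = 162 to 53 × 3 = 159). The second takes 1 (54 to 53). The envelope already records the physiotherapist, so no data collection changes.
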